**D. Project design**

D1. Design Summary

We propose a quality surveillance study of HEART Score implementation, including point-of-care i-STAT troponin testing, within the Forsyth, Stokes, and Surry County Emergency Medical Services (EMS) systems. Once, training is completed, we will pilot an implementation of the prehospital HEART Score. The pilot implementation cohort will accrue 500 patients being transported to WFBMC ED over the course of 1 year. For quality surveillance activities, participants will be identified retrospectively and data will be collected electronically using EHR (EMS records, and WFBH health records) and via telephone follow-up calls (which are customary in EMS quality assurance projects). As part of this pilot we will validate the i-STAT troponin for EMS use. We will obtain prehospital i-STAT troponin measurements on all 500 patients and compare results to in-hospital measurements on the same sample. These POC measurements will not be used for clinical care.

Prior to implementation, over 70 paramedics will be trained to use the Abbott i-STAT device for POC troponin analyses and to calculate a HEART Score. Following completion of the educational sessions, we will begin implementation in 18 ambulances across Forsyth County, Surry County, and Stokes County. During this pilot, paramedics will deliver care via their normal chest pain triage and destination plans, which includes obtaining an IV, ECG, and the administration of aspirin, nitroglycerin, and supplemental oxygen. Troponin and HEART Score results will only be conducted on patients previously determined to be transported to WFBMC ED. Paramedics cannot be blinded to POC troponin results, but these results will not be used to determine or alter the destination hospital for transportation or to deviate from existing triage and destination plans. Paramedics will communicate POC troponin results to the ED staff at WFBMC using a study specific form, which clearly states that this POC troponin value is for study purposes only and is not to be used to determine a patient’s clinical care. We will train ED nurses and providers that EMS POC troponin results are part of a pilot, should not be acted on clinically at this time, and require confirmation with a core-lab troponin. Furthermore, we will emphasize that while prehospital troponin testing is meant to speed recognition of ACS it is not intended to supplant in-hospital testing. WFBMC ED attendings will be blinded to the paramedic’s HEART score to assess inter-observer agreement.

D2. Study Setting

To improve the quality of care for patients with acute chest pain within Forsyth, Surry, and Stokes Counties, county EMS medical directors (Drs. [name], [name], and [name]) as well as the EMS Medical Director for the state of North Carolina ([name]) support a prehospital pilot implementation of the HEART Score including POC troponin testing beginning in 2016. Forsyth County EMS has approximately 80 medics, 16 ambulances in service, and completes about 35,000 transports annually. Stokes County EMS has 34 medics, 5 ambulances, and completes 6000 transports each year. Surry EMS has 73 medics, 7 ambulances, and completes approximately 17,000 transports annually.

During this pilot we are limiting participation to patients transported to WFBMC. This project will not change EMS triage and destination plans to alter a patient’s transportation destination and will not change care once the patient arrives to WFBMC ED. The rationale for limiting inclusion to WFBMC patients is: a) it will allow greater oversight of paramedic activities, as all of the investigators involved are employed at WFBMC and all ED faculty and residents have been trained to calculate and interpret HEART Scores and b) it will enhance our ability to assess the accuracy of paramedics’ risk assessments, because index and follow-up data will be collected retrospectively from the electronic medical record (EMR). WFBMC is a tertiary care center with 821 licensed beds, full specialty and subspecialty availability, and full cardiac catheterization lab capability. The ED has 47 beds, is a level 1 trauma center for adults and pediatrics, and has an annual volume of >100,000 visits. The ED is staffed by board certified or board eligible emergency physicians 24 hours per day, 7 days a week who directly provide care and oversee care provided by residents and midlevel providers. The ED Clinical Decision Unit (CDU) is also open continuously, has 18 beds, and is staffed by midlevel providers and supervised by attending emergency physicians. The CDU operates on algorithm-driven care for a limited number of specified complaints such as chest pain. The only route of admission to the CDU is through the ED and the ED attending has ultimate responsibility for all decisions made in the CDU.

D3. Subject Selection and Withdrawal

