## A3. Purpose of the Project Protocol

The objective of this pilot project is to establish the feasibility and accuracy of prehospital HEART score assessment using an Abbott’s i-STAT^®^ point-of-care troponin assay. If feasibility and accuracy can be established, the HEART score and POC troponin testing will allow modification of triage and destination plans so that patients can be transported to the most appropriate hospital settings as part of a larger implementation evaluation and to speed the delivery of ACS care. For example, patients with positive troponins and high HEART scores could be triaged to facilities with on-site cardiac catheterization laboratories, avoiding costly and inefficient inter-facility transfers. Furthermore, early risk stratification with the HEART Score, is likely to result in downstream efficiency gains; decreasing the ED length of stay for patients with low-risk chest pain.

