*i-STAT validation in moving ambulance:*, A validation of the i-STAT POC troponin assay in a moving ambulance will be performed. Previous study of the Abbott i-STAT POC troponin device showed high correlation between results in a moving ambulance compared with a laboratory environment. However, this is a small study and local validation is required before our paramedics and ED physicians use POC troponin results to influence clinical care. The first step of the i-STAT device validation will be to measure QC samples in a moving ambulance. Next, we will validate whole blood samples from all 500 patients by comparing i-STAT and central lab troponin results. These patients will have testing from the same blood draw with the Abbott i-STAT troponin assay in the ambulance followed by testing with the central lab assay: AccuTnI+3 assay (Beckman Coulter, California) or TnI-Ultra assay (Siemens, Munich Germany). The assay will be considered validated if the agreement between POC and central values (on “elevated” or “normal” results) in QC and patient samples is excellent; as defined by a kappa value >0.74. Validation will be done concurrent with the pilot implementation. The central lab troponin measurement will be run on whole blood obtained at the same time as blood used for the prehospital i-STAT. Please see Appendix 2 for the WFBMC Laboratory purposed method validation and quality control plan.*HEART Score Implementation Pilot:* Prior to implementation, over 70 paramedics will be trained to use the Abbott i-STAT device for POC troponin analyses and to calculate a HEART Score. Educational sessions will train the paramedics to correctly identify subjects appropriate for inclusion in the pilot and to correctly calculate a HEART Score. The educational tools will include in-person teaching and may include self-learning. Similar teaching methods and modules that have been used in the HEART Pathway Implementation (PI [name]) will be used in these sessions. Training regarding use of the Abbott i-STAT device will be conducted by Abbott Laboratories Inc. trainers. This will include the proper storage, maintenance, and use of device cartridges, quality assurance checks, and the interpretation and reporting or results. In addition to initial training, Abbott will provide full training and competency support for 1 year. Training and competency events for all testing personnel will be conducted at start-up, at 6 months, and at 12 months. Documentation of training and competency will be completed. There is no intent to publish this quality control data.

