*Rationale for not blinding paramedics and ED physicians to POC troponin results*: This is a clinical implementation pilot with a goal of testing the feasibility and accuracy of HEART score assessment using POC troponin results. A troponin result is a required component of the HEART score. Therefore in order to calculate a HEART score paramedics cannot be blinded to POC troponin results. Furthermore, through this implementation project we hope to gain greater understanding of the barriers and facilitators of a real-world implementation of the HEART score and POC troponin testing in a prehospital environment. Therefore, our implementation must closely match the expected paramedic workflow. In addition, we believe that asking unblinded paramedics to not share POC troponin results with receiving ED care team is unethical. In some patients POC troponin testing in the prehospital setting may provide early recognition of an acute myocardial infarction (non-ST-segment elevation myocardial infarction) and medics will be ethically compelled to share this information. However, since the POC troponin results are part of a pilot and their accuracy has not yet been confirmed, the paramedics will share results using a study specific form, which clearly states that this POC troponin value is for study purposes only and is not to be used to determine a patient’s clinical care. We will train ED nurses and providers that EMS POC troponin results are part of a pilot, should not be acted on clinically at this time, and require confirmation with a core-lab troponin. It is important to note that patients will already be receiving standard care for a possible NSTEMI. As part of their existing chest pain triage and destination plans paramedics will already be delivering standard care for acute myocardial infarction (aspirin, supplemental oxygen, and nitroglycerin). ED providers also routinely give patients with chest pain and possible NSTEMI aspirin, supplemental oxygen, nitroglycerin, and in high-risk cases use anticoagulation and antiplatelet therapy.

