## E. Project Procedures

## E1. Clinical Data Collection

For quality assurance data collection, participants will be identified retrospectively and data will be collected electronically using EHR (EMS records, and WFBH medical records) and via telephone follow-up calls.

Paramedics will use a worksheet to obtain the historical and clinical data needed to calculate a HEART score and this will include recording the POC troponin results. This worksheet will be an investigational record integrated into their normal reporting workflow. Data entered on this worksheet will be abstracted retrospectively. Data obtained will include demographic information (age, gender, race, ethnicity), date and time elements, characteristics of chest pain, ECG interpretation, cardiac risk factors (such as, prior coronary artery disease, smoking, hypertension, diabetes, hyperlipidemia, etc), POC troponin value, and the HEART score.

Since all participants will be transported to WFBMC ED, where the HEART Pathway is part of standard care, we will use the electronic medical record (EMR) to obtain ED physician HEART Score assessments and WFBMC troponin results. These data will be compared to paramedic assessments for determination of inter-observer agreement and correlation. We will also use the EMR to track index outcomes and 30 day events that occur within the WFBH system. Data collected from the WFBH EMR will include patient demographics, history and physical examination data, past medical history, cardiovascular risk factors, ECG results, laboratory results, HEART score and HEART Pathway assessments, ED and discharge diagnoses, disposition, index visit length of stay, objective cardiac testing at the index visit or within 30 days, recurrent ED visits, re-admissions, coronary revascularization, and MI or death within the follow-up period.

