**F. Statistical Plan**

F1. Overview

The primary concept of the PARA-HEART project is to evaluate whether paramedics can be taught to calculate a HEART score accurately with acceptable intra-observer reliability (when compared to ED physician assessments). This project is a clinical pilot study in order to generate data to support a larger and non-observational implementation. If we are able to show that these scores can be reliably predict MACE and agree with ED physicians assessments, then we can start using the HEART score in the pre-hospital setting to alter care and transport triage and destination plans.

F2. Sample Size and Power

The PARA-HEART project is a clinical pilot study in which we hope to demonstrate that paramedics are able to achieve 98% sensitivity for the detection of MACE. To achieve a sensitivity of 98% with a lower bound of the 95% confidence interval that exceeds 90% we will need at least 50 patients with MACE events. Assuming a 10% MACE rate among our chest pain population,[^4-7^](#_ENREF_4) to include 50 patients with adverse events we will need a total sample size of 500 patients.

F3. Analysis Plan and Statistical Methods

The percentage of patients identified by paramedics using the HEART Score with POC troponin testing as high- and low-risk, the sensitivity, specificity, and positive and negative predictive values, positive and negative likelihood ratios, and accuracy for MACE will be calculated. Corresponding 95% exact binomial confidence intervals will be computed.

The proportion of patients receiving objective cardiac stress testing, cardiac catheterization, myocardial infarction, or cardiac death during the index hospitalization will be estimated for subjects classified as high and low risk by ED physicians and compared with those classified as high and low risk by paramedic assessment. Cardiac-related ED visits and readmission to the hospital will be calculated at 30 day follow-up. LOS will be reported using descriptive statistics, including median and inter-quartile range as this outcome tends to have a nonparametric distribution.

HEART scores calculated by the blinded primary ED provider will be compared to the HEART scores obtained by the paramedics. Raw percent agreement and kappa scores will be determined to assess intra-observer reliability. A kappa of >0.75 will be defined as excellent agreement, 0.60-0.74 will be defined as acceptable agreement, and <0.59 will be defined as unacceptable agreement.

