*Hematocrits in the range of 0-65% PCV have been demonstrated not to affect results. Samples with hematocrit levels above this range have demonstrated increases in the test imprecision and quality check codes.*

*The analyzer must remain on a level surface with the display facing up during testing. Motion of the analyzer during testing can increase the frequency of suppressed results or quality check codes. A level surface includes running the handheld in the downloader/recharger.*

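### Feasibility is named first in the objective, but no outcome records how often a paramedic obtains a valid troponin and a complete HEART score, and the plan assumes a result in all 500 patients

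*Protocol*

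**What the plan says.** Section A3 opens: "The objective of this pilot project is to establish the feasibility and accuracy of prehospital HEART score assessment". The Abstract (A1) says that feasibility has to be shown from surveillance data before the score and troponin are built into triage and destination plans.

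The plan counts on complete ambulance testing. D1 has "We will obtain prehospital i-STAT troponin measurements on all 500 patients", and D4 has "Next, we will validate whole blood samples from all 500 patients by comparing i-STAT and central lab troponin results". D4 also notes that "A troponin result is a required component of the HEART score". The assay sheet in K2 (Test Limitations) asks for a level surface during testing and warns: "Motion of the analyzer during testing can increase the frequency of suppressed results or quality check codes".

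E2 lists 30-day MACE as the primary outcome, with cardiac testing, length of stay, hospitalization and cardiac-related return visits as secondary outcomes. F3 adds the high- and low-risk percentages, diagnostic accuracy with exact binomial intervals, and kappa against the ED provider. F4 covers missing outcome data only. On cohort formation, E1 says that "participants will be identified retrospectively".

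**The concern.** Sensitivity, predictive values and kappa can be computed only where a score exists. None of them shows in how many transports the paramedic obtained a valid troponin and finished the score before hand-over. The device validation in D4 has the same gap: it is a kappa on elevated versus normal results, and a suppressed result is neither.

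The cohort definition does not close the gap. Nothing states whether the 500 are eligible transports, transports in which the test was attempted, or transports with a completed score. Nor does the protocol say how a patient without a paramedic troponin is handled.

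At stake is the decision the pilot is meant to inform. A tool that works well when it works, but often gives no result, could pass every criterion in F3 and be taken forward as feasible. Its accuracy would then describe successful tests, not all patients to whom a changed triage plan would apply.

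**Working it through.** **1. The plan's own figure.** F2 wants "a lower bound of the 95% confidence interval that exceeds 90% we will need at least 50 patients with MACE events" at 98% sensitivity, and continues "Assuming a 10% MACE rate among our chest pain population". Total N = 50 / 0.10 = 500, which reproduces. It holds only if every patient has a usable ambulance result.

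**2. Precision with no failures.** F3 specifies exact binomial intervals. One missed MACE in 50 gives 49/50 = 98.0%, with an exact (Clopper-Pearson) 95% lower limit of 89.35%. That is already below 90%.

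**3. Two readings of the 500.**
- *Completed scores:* 500 scored patients and about 50 MACE. No precision is lost, but the failed encounters lie outside the cohort and are never counted.
- *Eligible or attempted transports:* failures can be counted, but fewer than 500 patients have a score.

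The two consequences belong to different readings and cannot be added together.

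**4. Size under the second reading.** The documents give no failure rate, so f is an assumption. Failure is also assumed unrelated to MACE. Scored patients = 500(1 − f); scored MACE = 0.10 × 500(1 − f). The completion interval is the exact 95% interval for scored/500. Sensitivity is shown with one miss, on whole events (47.5 taken as 47).

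| Assumed f | Scored (exact 95% CI for completion) | Scored MACE | One miss | Exact lower limit |
|---|---|---|---|---|
| 5% | 475 (92.7% to 96.7%) | 47.5 | 46/47 = 97.9% | 88.7% |
| 10% | 450 (87.0% to 92.5%) | 45 | 44/45 = 97.8% | 88.2% |
| 20% | 400 (76.2% to 83.4%) | 40 | 39/40 = 97.5% | 86.8% |

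At f = 10% the lower limit falls from 89.35% to 88.2%, about 1.2 points. With no miss, the lower limits are 92.5% (47/47), 92.1% (45/45) and 91.2% (40/40).

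**5. How the handling of unscored patients moves sensitivity.** Take 50 MACE in the whole cohort and one miss among the scored.
- f = 10% (5 unscored MACE): completed scores 44/45 = 97.8%; unscored counted as not low-risk (44 + 5)/50 = 98.0%; unscored MACE counted as missed 44/50 = 88.0%.
- f = 20% (10 unscored MACE): 39/40 = 97.5%; (39 + 10)/50 = 98.0%; 39/50 = 78.0%.

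Counting unscored patients as not low-risk raises sensitivity and lowers specificity. Counting unscored MACE as missed lowers sensitivity. The gap is 10 points at f = 10% and 20 points at f = 20%, so the choice matters far more than the loss of precision in step 4.

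**The case against.** The strongest reply is that feasibility is defined. Section J1, under human subjects involvement, glosses it as the accuracy and reproducibility of the paramedics' score. F3 measures both, and D4 and K2 add assay validation with QC samples run in a moving ambulance. The primary hypotheses and primary outcome concern sensitivity, predictive value, kappa and MACE, not completion. This stands to the extent that feasibility is not wholly undefined. It does not answer the point, because accuracy and reproducibility can be measured only where the test was completed.

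A reader might infer that the protocol drops failed tests. It does not say so: D3 does not require a valid troponin, and retrospective identification describes data capture, not selection on a completed score. Detailed handling could also sit in an analysis plan that is not shown. What the protocol itself fixes is the premise of a result in every patient, a sample size without allowance for failures, and an outcome list without a completion measure.

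A reader might also infer that motion makes the test fail. K2 says only that it can increase suppressed results, and it counts running the handheld in its recharger as a level surface. The protocol cites earlier work on testing in moving ambulances, plans repeated training, and excludes transports with under 5 minutes of anticipated scene plus transport time. These may keep the failure rate low, but the planned outcomes would not show it.

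**Conclusion.** The point holds as a gap in what is measured. The protocol makes feasibility a condition for changing triage plans, but no stated outcome captures how often the ambulance test and score can be completed. The premise of a result in all 500 patients sits uneasily with the assay sheet's own warning.

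Its size cannot be fixed from the documents. Under assumed failure rates of 5% to 20%, unrelated to MACE, a cohort of 500 eligible or attempted transports would yield 475 to 400 scored patients and about 47.5 to 40 scored MACE.

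The stronger reading, that failed tests push sensitivity below the 90% bound, is not supported. With one miss in 50 and no failures, the exact lower limit is already 89.35%; with no miss, it stays above 90% at all three assumed rates. Failures worsen an existing shortfall and do not create it. The main harm is that failure would go unmeasured and that accuracy might describe successful tests only. This is a cheap improvement worth making, not a fatal flaw.

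**What to change.** - **D1, E2 and F3:** define the 500 as eligible transports, or at least attempted tests, identified from the EMS records and worksheets already in use. Add a feasibility outcome: the proportion with a valid point-of-care result and a complete HEART score, with an exact 95% interval.
- **F3:** report accuracy in completed scores and, beside it, in the whole cohort under both bounds: unscored patients counted as not low-risk, and unscored MACE counted as missed. Neither bound should stand alone.
- **D1 and D4:** replace the statement that all 500 will have a result with one that testing will be attempted in all 500.
- **F2:** state that the 50 events assume no failed tests, and show the expected scored MACE at assumed failure rates. If the sponsor wants to keep 500 scored patients, the cohort would need 500/0.95 = 527, 500/0.90 = 556 or 500/0.80 = 625 (rounded up).

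The cost is some further record abstraction and a second and third 2×2 table. Retrospective eligibility will be imperfect, because it rests partly on the paramedic's judgement of symptoms and anticipated time. Specificity or sensitivity will look less favourable in the bounding analyses. No new patient procedure is needed.
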